### Smoking cessation: therapeutic barriers and positive effects on mental health

1.3

While progress in the general understanding of SUD is necessary, smoking cessation interventions also offer a worthwhile way to improve outcomes in SUD treatment concerning physical health. Moreover, evidence suggests a therapeutic surplus value, as evidenced by improved mental health and favourable effects on reward processing (8, 10, 40). Nonetheless, smoking cessation interventions are not implemented widely and systematically in SUD treatment (41). Studies show that only modest percentages of SUD patients are reached by smoking cessation programs due to misconceptions of clinicians and organizational barriers such as limited training, lack of resources, and cultural norms that do not recognize smoking cessation as part of the therapeutic mission. Smoking in staff, therapeutic nihilism in mental healthcare workers, and subjective theories that smoking cessation concurrent with other alcohol or drug treatment may create a risk to sobriety were reported (41–43). The self-medication hypothesis, assuming that smoking can relieve stress and other symptoms related to poor mental health, is another influential belief (7).

However, empirical research shows a very different picture: tobacco smoking goes along with a repetitive vacillation of mood states (44). Smoking deteriorates mood and causes anxiety as well as stress and withdrawal symptoms rather than reducing them (45). As these feelings are reliably (yet temporarily) relieved by smoking, this creates the perception that smoking has psychological benefits, while, in fact, it is smoking that causes psychological disturbances in the first place. Thus, smokers seem to misattribute the ability of cigarettes to abolish nicotine withdrawal as a beneficial effect on mental health (40, 44). A growing body of evidence underlines this effect: starting to smoke increases mental illness parameters such as depressive and psychotic symptoms, anxiety and stress and is even a predictor of suicide attempts (46–48). Conversely, smoking cessation has been reported to improve a variety of mental health parameters in meta-analytic research, namely anxiety, depression, perceived stress, and positive affect. Concerning improved mood, as well as reduced anxiety and stress, the effect size of smoking cessation is comparable to the effect size of serotonin reuptake inhibitors and might thus, indeed, be therapeutic (7, 40).

### Gateway effects of nicotine on brain reward circuitry

1.4

Effects of nicotine on the brain’s reward system have been studied extensively under the assumption that it might act as a ‘gateway drug’. The gateway hypothesis posits that certain substances lower the threshold for addiction to other, more severe psychoactive substances. The evidence supporting such effects of smoking is compelling (8, 49). It was found that nicotine increases dopamine release in the brain’s reward circuitry through functional alterations in the *nucleus accumbens* and the ventral tegmental area. This change enhances neural reward sensitivity, making individuals more susceptible to other drugs by promoting synaptic plasticity. The mechanisms involved herein include epigenetic modifications, such as histone acetylation, which influence the expression of certain genes, including the transcription factor ΔFosB, in reward neurons. Additionally, alterations in mesolimbic receptor systems, including nicotinic acetylcholine and AMPA receptors, as well as GABAergic inhibition, are also involved. Altogether, these molecular changes can lead to long-term structural and functional adaptations in neural networks, increasing the propensity for subsequently administered substances like cocaine (8). The relevance of these molecular mechanisms is underpinned by behavioural evidence from experimental animal research and epidemiological data. Levine and colleagues experimented with a combined gavage of nicotine and cocaine in mice and reported dramatically increased addiction-related behaviours such as conditioned place preference and locomotor sensitization (49). In human cocaine-naive users, it was found that regular smokers had a markedly higher probability of developing an addiction to cocaine. There is also evidence for increased reward and addiction to alcohol, psychostimulants, cannabis, and opioids through nicotine, and the maturing brain during adolescence seems to be especially vulnerable to these effects (50). Further support for gateway effects of nicotine derives from large-scale epidemiological data from annual US nationwide surveys. Here, it was found that smoking rates declined in parallel with non-medical drug use. It was reported that the decline resulted from the growing group of non-smokers, and their levels of non-medical drug use were at least four times lower than those of smokers (51).

While these mechanisms are well-documented, from the molecular to the epidemiological level, their findings seem to be hardly perceived in clinical contexts. Also, the role of nicotine in trajectories of SUD remains largely unclear, and it is currently unknown to what extent the effects of nicotine on reward processing are reversible. The reversibility of nicotine’s effects on reward processing is a critical question for this study, which hypothesizes that reversing gateway mechanisms may mitigate addictive factors and lead to improved outcomes in SUD treatment.

### Associations between primary emotions, self-efficacy reward processing, and SUD treatment outcomes

1.5

It seems plausible but is currently speculative that the negative influence of nicotine on the brain’s reward systems might be reversed by smoking cessation. Whereas meta-analytic research clearly links smoking cessation to improved mental health (40), other studies suggest that this is due to alterations in emotional states, such as reduced emotional fluctuations and changes in the experience of positive and negative emotions over time (44, 52). Smoking affects nicotinergic and dopaminergic pathways in subcortical brain systems (45) which are involved in the biological foundations of primary emotions. Several findings point to associations between primary emotions, cigarette smoking, and addictive behaviour in general (53, 54). It is thus believed that primary emotions play an important role in SUD by influencing the regulation of stress and reward systems and have at least a mediating effect on substance craving and addictive behaviour (53).

However, the relationship between smoking cessation and primary emotions warrants further empirical investigation. Consideration of metabolic and gut microbial mechanisms may also bring further elucidation regarding this association.

### Pilot study: Fuchshuber et al. (2024)

1.6

A recent pilot study from our research group showed significantly increased self-efficacy in individuals with SUD following a 6-week smoking cessation intervention during an inpatient stay within the setting of a therapeutic community, going along with reduced consumption of cigarettes per day (55).

Longitudinal data from the tobacco cessation intervention (IG) vs treatment-as-usual control group (TAUG), group x time interaction effects showed significantly improved self-efficacy (2 x 2 ANOVA: *F*(1,53) = 5.86; *p* <.05; η_p_^2^ = .11) and decreased consumption of cigarettes per day (GEE: Wald-χ2 = 4.72, *df* = 1, *B* = 1.16, *p* <.05) in the intervention group (see **Figure 1**). While this pilot study had some limitations (pre-post design without randomization; no follow-up examination; lack of power), decreased general substance craving trends were also observable. This may be related to the aforementioned therapeutic effect of nicotine cessation, which could potentially reduce general addictive factors and improve SUD outcomes through biological and psychological mechanisms, including alterations in metabolic and gut microbial factors, brain reward processing, primary emotions, and perceptions of self-efficacy.

**Figure 1 f1:**
[figure not shown]
Results of the pilot study examining the effects of smoking cessation in SUD patients Left: Significantly interaction effect in self-efficacy (group x time); Right: Significantly decreased consumption of cigarettes per day; Decrease in general substance craving is more pronounced in the IG than in the TAUG by tendency (p = .18).

### Neural, metabolic, and gut-microbiome-mediated pathways of nicotine on affect and reward

1.8

#### Mesolimbic nicotinic receptor systems

1.8.1

There is evidence that the direct actions at nicotinic acetylcoline receptors (nAchRs) of nicotine and its metabolites can increase negative affectivity, downshift hedonic set points, and increase sensitivity to social defeat stress (58). The neuroadaptions in nicotinic pathways in the brain caused by chronic smoking are associated with occurrence of depressed mood, agitation, and anxiety shortly after a cigarette is smoked (40). Experimental studies suggest a sensitization to negative emotional cues during nicotine withdrawal (52, 59). Functional alterations of the reward system are also supported by brain imaging studies (60). The fluctuations in the psychological state of smokers are known as the withdrawal cycle. The upregulations of nAchRs, and withdrawal symptoms were found to return to normal levels by three weeks after smoking cessation (61, 62).

Negative emotions, particularly in the absence of emotion regulation strategies, are often preceding substance misuse (53). The role of negative affects is also stressed by an influential addiction theory, which posits that escape and avoidance is the prepotent motive for drug use (57).

#### Oxidative stress, lipid and inflammatory pathways

1.8.2

A multi-omics study compared metabolite levels between cigarette smokers, e-vapers, former smokers and never smokers (27). Metabolic concentrations showed distinct smoking dose-dependent distributions of elevated inflammation markers and pathways. In smokers, apart from nicotine and its downstream metabolites, metabolites derived from toxicants (e.g. p-cresol sulfate), increased metabolites of oxidative stress and detoxification pathways (pathways of gluthatione conjugation) were found. Lower caroten-diol levels indicated oxidative depletion of antioxidants. Oxidative stress responses are known to be associated with exacerbation of withdrawal symptoms and enhance reward seeking (63). Lipidomics analyses revealed increased concentrations in oxidized derivatives of polyunsaturated fatty acids (PUFAs). More precisely, eicosanoid derivates such as 14,15DHET or 9-HODE, known to be involved in inflammatory signaling, were elevated. Circulating CRP and haptoglobin were also increased, reflecting chronic inflammation in smokers. Strongly elevated levels of N-acetylputrescine were also observed, a metabolite related to polyamine metabolism and influencing cell proliferation, immune function, and stress responses (27). Similar and confirmatory patterns of increased inflammatory activation with elevated CRP and interleukin-6, and lipid profiles (cholesterol, triglycerides, LDL) in smokers vs. controls were recently published (64).

Activation of oxidative and cell stress, and lipid inflammatory pathways are linked in complex ways to reward circuitry. There is evidence for associations with blunted reward and increased propensity for immediate gratification via dopamine pathways in the nucleus accumbens and medial prefrontal cortex, but also increased negative affectivity, learned helplessness, and proneness for depression (65, 66).

#### Gut microbiome pathways: SCFA, tryptophan, and bile acids

1.8.3

Few small studies have directly examined the effect of smoking cessation on the microbiome (67, 68), but there is a growing body of evidence for general smoking-associated gut microbial alterations (69). A large mendelian randomization study provided mechanistic insights for a cross-talk and causal relationship between bacterial species and smoking behavior. Fan et al. (28) reported that lower abundances of *Actinobacteria* may cause increased smoking, with a potential positive feedback effect (further lowered abundances of *Actinobacteria* by smoking). Bacterial species and also belonging metabolic pathways were identified: *Actinobacteria* and *Peptococcus* were associated with alterations in tryptophan and tyrosine metabolites, and *Peptococcus* with effects on valerate (a short-chain fatty acid SCFA). The authors concluded, that these bacteria, via the identified metabolites, play a causal role in the action pathway from the gut microbiome to smoking behavior (28).

Tryptophan metabolism, and the downstream kynurenine pathway is a key metabolic pathway in the broader addiction literature (70). It is known that drugs of abuse dysregulate tryptophan metabolism and kynurenine metabolite concentrations via oxidative stress and immune responses, with immediate effects on the dopamine reward system. A recent study provided additional evidence for disturbances of tryptophan and kynurenine metabolism through smoking (71). Disrupted kynurenine pathway metabolism was also found in depression (72), altogether pointing to shared pathways of affect and reward in addiction and other psychiatric conditions.

Short-chain fatty acids (SCFA) are produced by the bacterial fermentation of dietary fiber, and are known as key gut-brain signaling mediators with a high relevance for reward and addiction (73–75). SCFA are lowered in smokers via gut microbial effects (76). They have anti-inflammatory properties, protect against oxidative stress and modulate transcriptional regulation in the brain. SCFAs exert epigenetic effects, stimulating memory and synaptic plasticity by inhibiting histone deacetylases (HDAC) or modulating DNA methylation, thereby altering the expression of addiction- related genes (*e.g.*, CREB transcription factor, c-Fos, dopamine receptors and μ-opioid receptors) and persistently reshaping reward circuit plasticity (77).

Recent studies point to elevated cholesterol and disruptions in bile metabolism (associated with microbial alterations) induced by smoking (64, 78). Bile acids are known agents of gut-brain signaling, and disruptions in bile acid profiles were found in humans with anxiety and depression (79, 80).

#### One-carbon metabolism: methylation as a mediator of reward

1.8.4

One-carbon metabolism, with primary methyl donors such as choline and folate, is also implicated in the biology of SUD (14). These compounds are vital for epigenetic regulation of learning mechanisms, and have been shown to impact responses to substances of abuse (81, 82). Smoking goes along with lower choline levels, higher homocysteine, and generally altered one-carbon metabolism (83, 84). Nicotine can indirectly influence cellular methyl group metabolism by altering the expression and activity of DNA methylation machinery, which affects the utilization of methyl donors like S-adenosylmethionine (SAMe). For example, nicotine exposure down-regulates DNA methyltransferase (DNMT) gene expression and reduces global DNA methylation in human cells, a process that may reflect changes in methyl group availability or DNMT demand for SAMe-dependent methylation reactions (85). Decreased methylation capacity is implicated in reward and stress pathways (14, 86). Choline is also the precursor of Acetylcholine, a neurotransmitter central to emotion, attention, and reward. Low choline and Acetylcholine are linked to anxiety, inflammation-related mood dysregulation, and altered dopaminergic reward signaling (87, 88).

The gut microbiome is an important player with regard to choline metabolism, as choline is consumed by gut microbes to produce TMA, which limits host choline bioavailability. The amount of microbial TMA production depends on microbiota composition, influencing choline and related one-carbon metabolites in the host (89, 90).

## Research aims

2

The present study attempts to clarify the mechanisms of action and therapeutic outcomes in SUD patients undergoing a 6-week behavioral smoking cessation program during their stay within the setting of a drug-free therapeutic community. The study aims to examine the mechanisms of action and therapeutic outcomes in three domains: the psychobehavioural domain, the metabolic domain, and the gut microbial domain. The existence of an additional fourth latent domain, namely reward processing, is assumed. As the causal interconnections between the domains and single variables are complex and innovative (see **Figure 2**), the investigations will be driven by clear hypotheses but will as well be largely of exploratory character.

**Figure 2 f2:**
[figure not shown]
Hypothesized causal relations and interconnected mechanisms related to smoking cessation and SUD on metabolic, gut microbial, and psychobehavioural levels. Brain reward circuitry (‘gateway’) effects are also hypothesized but only indirectly observable (latent).

### Study objectives

2.1

#### Psychobehavioural domain

2.1.1

In line with previous empirical findings from our pilot study and the research literature, we hypothesize changes in primary emotions, self-efficacy, and general substance craving (7, 10, 55). More precisely, we assume increases in positive emotions and decreases in negative emotions, greater emotional stability, and reduced psychiatric symptom burden post-intervention. Reversed gateway effects of nicotine on reward processing may contribute to these results due to shifts in neurotransmitter systems and mesolimbic and mesocortical pathways (8, 45). Based on empirical observations and theoretical frameworks of inference of allostasis, we further hypothesize that enhanced self-efficacy facilitates sustained behaviour change, reducing reliance on maladaptive coping strategies, resulting in reduced general substance craving, nicotine addiction, and reduced clinical relapse rates after smoking cessation. The secondary aim of the study involves replicating and extending the findings from our previous study (55). This includes the examination of the clinical long-term outcome and success of the smoking cessation intervention as reflected in group differences at 3-month follow-up.

#### Metabolic domain

2.1.2

The notion of addiction as a metabolic disorder requires further investigation in human subjects and in the clinical field, which represents an emphasis of investigation in this study (14, 16). Analyses will be performed with regard to metabolic profiles in SUD patients during their inpatient-stay in a drug-free therapeutic community and the additional contrasting between-group effects of smoking cessation. While the examination of metabolic factors is largely exploratory, particular attention will be paid to metabolic markers and cluster analyses corresponding to psychiatric symptoms, as well as to pathways of choline and folate metabolism. Metabolic correlates of primary emotions and psychiatric symptoms will be identified in exploratory analyses. In line with previous research, we hypothesize that smoking cessation goes along with increased choline levels and altered choline/folate metabolism (14). Downstream analyses will be focused on metabolites of immune and inflammatory regulatory pathways, oxidative stress, neurotransmitter precursors and metabolites and enzymes (tryptophan, kynurenic and quinolinic acid, indoleamine-2,3-dioxygenase, and tryptophan-2,3-dioxygenase).

#### Gut microbial domain

2.1.3

In line with previous studies, we hypothesize that smoking contributes to gut microbial imbalances, reduced general bacterial diversity and abundance of commensals, and growth of pathogens (91). We hypothesize that reversed effects in these imbalances will be observable after smoking cessation. Further emphasis will be put on the identification of microbial markers corresponding with general substance craving, history of smoking and success of smoking cessation. Gut microbial correlates of primary emotions and psychiatric symptoms will be identified in exploratory analyses. Analyses will further focus on bacterial genera with a known role (as derived from literature) in the metabolism of SCFA, PUFA, bile acids, and tryptophan (metabolites) (20). Combined metabolome-microbiome analyses will ascertain associations between bacterial abundances and concentrations of relevant metabolites.

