A-priori sample size calculations were performed with G-Power (108) (version 3.1.9.6), for a mixed-design ANOVA with one interaction between group (2 groups) and assessments (2 repeated measurements). Considering the effects mentioned above, the mixed-design ANOVA was set rather conservatively for a medium effect size (Cohen’s F = 0.25), a statistical Power (1-β) of 0.9, a α of 0.05, an intra-correlation coefficient of 0.5 and nonsphericity correction of 1, resulting in a minimum sample size of 46 subjects per group, and a critical F = 4.06. Adjusting for expected attrition of about 10%, a total sample size of size of 100 is set. The many (mostly biological) variables measured in this study will expectably require statistical corrections; this will also be compensated by statistical methods exceeding classical linear approaches, namely machine learning feature detection and modelling methods (109).

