#### Controlling for potentially confounding variables, and multiple testing

4.7.3

Proper analysis of the research questions in the SUD sample will be hampered by several sources of variance, such as diet, psychiatric diagnoses, medications, and history of substance misuse. These variables will be held constant as control variables.

Psychiatric comorbidity is highly present in the population. Psychiatric symptom burden and classes of psychiatric diagnoses are associated with systematic metabolic and microbiome profiles (72, 113, 114). Classes of psychiatric secondary diagnoses (mood, anxiety, psychotic, and neurodevelopmental disorders) will therefore be considered as covariates. Intake of psychotropic medications are respectively frequent. The literature shows reciprocal interactions between psychotropic medications and gut microbiota (115), and metabolic patterns in response to treatment (116, 117). Type of medication class intake (antipsychotics, antidepressants, antianxiety drugs, anticonvulsants/mood stabilisers, opioid substitution) will be considered as covariates. Length and consumption patterns from SUD history will also enter covariate analysis (with regard to substances – primarily consumed substances vs. polytoxicomania). These covariates will be entered in Multi-omics factor analysis (MOFA) in direct joint modeling (118) to ensure that observed microbiome–metabolome–psychological associations are not driven by covariate effects. For the microbiome domain, intervention vs. control group comparisons regarding microbial abundance and composition will be performed with Analysis of Compositions of Microbiomes with Bias Correction (ANCOM-BC), a package which allows for continuous and categorical covariate adjustment within a linear regression framework, and was designed to analyze longitudinal data (119).

Metabolome and microbiome studies involve the examination and statistical testing of a multitude of variables. Thus, controlling for multiple testing is a must; False Discovery Rate corrections will be based on statistical recommendations promoting flexible algorithms within the R package FDRestimation (120).

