#### Statistical analyses of psychological variables

4.7.4

The statistical analyses will be performed in SPSS version 29 (IBM) for general procedures, while specific regression models are handled in R (R core team (121)). For example, t-tests will be carried out for independent and paired comparisons of means between and within groups at different times, respectively, assuming that the continuous data are normally distributed. Chi-square and Fisher’s exact tests, the latter in cases of smaller sample sizes, will be conducted in order to test the associations between categorical variables. The Friedman test shall be used in analyzing non-parametric repeated measures. The main effects of the intervention, time effects, and group x time interaction will be tested using a 2 × 3 two-way repeated measures ANOVA design (group x time), using the Greenhouse-Geisser correction in cases when the sphericity assumption will be violated. The level of significance will be α = 0.05, two-tailed, using Bonferroni adjustment for multiple comparisons. In addition, a repeated measures proportional odds logistic regression model using a generalized estimating equation (GEE) will be applied, assessing the intervention’s effect on CPD treated as an ordinal variable. The GEE model, computed in R using the `repolr` package (122), will contain robust variance estimators that take into account within-subject correlations (**Table 2**).

**Table 2 T2:** Summary of statistical methods and outcomes.

Outcome variable	Domain	Statistical method	Software
Self-efficacy, craving, psychiatric scores	Psychobehavioural	Repeated measures ANOVA, t-tests, Friedman test	SPSS
Cigarettes per day (ordinal)	Psychobehavioural	GEE (Proportional odds model)	R (repolr)
Bacterial diversity indices	Microbiome	Kruskal-Wallis, ANOSIM, db-RDA	R, QIIME
Taxonomic composition	Microbiome	MaAsLin2, ANCOM, LEfSe	QIIME2, R
Metabolite concentrations	Metabolic	PCA, O-PLS-DA, correlation analyses	NMR tools, R
Cross-domain associations	Combined (exploratory)	Correlation and regression	R

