
For beta diversity, db-RDA will be performed on Bray-Curtis, Jaccard, and UniFrac distance matrices (weighted and unweighted) to compare the structural similarities between groups’ microbiomes. Beta diversity indices will be visualized with PCoA plots using Bray-Curtis and Jaccard dissimilarities. The Firmicutes/Bacteroidetes (F/B) ratio will be calculated from the rarefied feature table. Using this, MaAsLin2 will be used to detect differentially abundant taxa and further test associations with variables of interest such as cigarettes per day or metabolic markers (126). Identifications of microbial biomarkers will then be done applying LeFSe both in longitudinal and cross-sectional comparisons. This will be furthered to detect significant differences between groups in the microbial taxonomic abundance using the Analysis of Composition of Microbiomes’ ANCOM-BC implemented within QIIME2 (119).

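### Taxon-metabolite associations are tied to a rarefied, constant-sum table, so a dominant taxon linked to a metabolite can make unrelated genera look inversely linked, and FDR correction does not remove this

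*Protocol article*

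**What the plan says.** - **Aim (2.1.3, Gut microbial domain):** "Combined metabolome-microbiome analyses will ascertain associations between bacterial abundances and concentrations of relevant metabolites". No scale or transform is named there.
- **Tool (4.7.5, Microbiome analyses):** the Firmicutes/Bacteroidetes ratio is "calculated from the rarefied feature table. Using this, MaAsLin2 will be used to detect differentially abundant taxa", and MaAsLin2 will "further test associations with variables of interest such as cigarettes per day or metabolic markers".
- **Table 2 (4.7.4), cross-domain row:** "Correlation and regression", labelled exploratory, with no input scale.
- **Composition-aware method (4.7.3):** "intervention vs. control group comparisons regarding microbial abundance and composition will be performed with Analysis of Compositions of Microbiomes with Bias Correction (ANCOM-BC"). Section 4.7.5 again uses it for differences between groups. Section 4.7.3 describes it as "a package which allows for continuous and categorical covariate adjustment within a linear regression framework".
- **Joint model (4.7.3):** MOFA with covariates is planned for associations across microbiome, metabolome and psychological data. Its input scale is not given.
- **Dry weight (4.7.6.2, stool NMR):** microbial abundances as well as metabolite concentrations are to be normalised to the dry weight of the stool. Section 4.7.5 describes 16S amplicon sequencing, with no qPCR, spike-in or cell count for total load.
- **Multiplicity (4.7.3):** FDR correction, with level and algorithm left open.

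**The concern.** Rarefying gives every sample the same read total, so each entry is a share. Shares have a common denominator: when a large taxon grows, every other share must shrink even if those taxa have not changed. If the large taxon follows a metabolite, the shrinkage follows it too, and unrelated genera acquire a negative association with that metabolite.

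On the share scale these associations are real, so their small p-values are not chance findings and FDR correction has no reason to reject them. They are wrong only as answers to the question in 2.1.3, which concerns bacterial abundances. The plan guards the arm comparison with ANCOM-BC but names no comparable protection for the metabolite associations. At stake is the interpretation of exploratory taxon-metabolite links in the SCFA, bile acid and tryptophan pathways.

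**Working it through.** The protocol gives no figure for this analysis, so there is none to reproduce.

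**1. Which table is used.** In 4.7.5, the sentence that introduces MaAsLin2 opens with a back-reference to the sentence on the ratio and the rarefied table. MaAsLin2 needs a table of taxa. A single ratio cannot yield differentially abundant taxa, so the rarefied table is the natural referent.

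**2. The mechanism in arithmetic.** Let the dominant taxon have share s and its absolute abundance rise by a factor k, with all else unchanged. Every other share is multiplied by 1/(1 − s + s·k). For a rise of one SD on the ln scale (SD 1.0 assumed), k = e = 2.718:
- s = 0.14: 1/(0.86 + 0.381) = 0.81, a fall of 19%
- s = 0.24: 1/(0.76 + 0.652) = 0.71, a fall of 29%
- s = 0.41: 1/(0.59 + 1.114) = 0.59, a fall of 41%

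In centred log-ratios, the common factor cancels. Only the dominant taxon's part in the mean log remains: with 61 taxa, 1/61 = 0.016 ln units, against ln(1.704) = 0.53 for shares at s = 0.41.

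**3. Simulation.** From the protocol: N = 100 and about 10% attrition ("Adjusting for expected attrition of about 10%, a total sample size of size of 100 is set"), so about 100 × 0.9 = 90 completers, and the 4.7.5 filter (20 counts, 5 samples). Assumed: one dominant taxon with log-SD 1.0, whose log abundance correlates rho with the metabolite; 60 genera independent of both; depth 10,000 reads; one time point; Spearman tests with Benjamini-Hochberg at 5%; 200 runs per setting. Results are for n = 100 with log-SD 1.0 for the other genera (1.5 in brackets). CLR is computed from the same rarefied counts.

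| Dominant share | rho | Mean false genera, shares | Realised FDR, shares | Realised FDR, CLR |
|---|---|---|---|---|
| 0.14 | 0.5 | 0.27 (0.28) | 0.12 (0.12) | 0.05 (0.04) |
| 0.24 | 0.5 | 1.7 (0.69) | 0.37 (0.23) | 0.05 (0.05) |
| 0.24 | 0.7 | 6.6 (1.3) | 0.70 (0.34) | 0.06 (0.08) |
| 0.41 | 0.3 | 2.2 (0.57) | 0.33 (0.20) | 0.05 (0.04) |
| 0.41 | 0.5 | 11.7 (2.9) | 0.77 (0.49) | 0.10 (0.08) |
| 0.41 | 0.7 | 33.0 (11.1) | 0.96 (0.84) | 0.14 (0.16) |
| 0.58 | 0.7 | 51.7 (27.9) | 0.98 (0.95) | 0.28 (0.33) |

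With rho = 0, realised FDR on shares is about 0.04 to 0.08, so there is no material inflation. Above a share of about 0.2, essentially all false links are negative. With n = 90, share 0.41 and rho 0.5, the mean is 10.3 false genera and FDR 0.74 (log-SD 1.0).

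**4. Second set of assumptions.** With n = 90, 79 unrelated genera and rho 0.4 to 0.6, realised FDR on rarefied shares is about 0.10–0.24 at a dominant share of 0.18, 0.22–0.54 at 0.28 and 0.46–0.74 at 0.38. Centred log-ratios of unrarefied counts give about 0.03–0.04.

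**5. Dry weight.** The number of 16S reads is set by sequencing and then by rarefaction, not by the bacteria present per gram. Dividing reads by dry weight therefore does not recover absolute abundance. A table so divided also no longer has the constant total of a rarefied one, so 4.7.5 and 4.7.6.2 cannot both describe the same input.

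**The case against.** **The text leaves room.** Section 2.1.3 names no scale, the back-reference in 4.7.5 could be read as the ratio, and MaAsLin2's normalisation and transform are not given. They may stand in an analysis plan that is not shown, and a log-ratio setting there would largely remove the problem. This stands as a limit on confidence. It does not remove the point, because 4.7.5 does name the rarefied table and would still need rewording.

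**The effect may be small.** This stands in part. With n = 90, 79 unrelated genera and rho 0.4–0.6, the mean number of false genera after correction is 0.25–0.7 at a dominant share of 0.19, and 0.55–1.5 at 0.24. Section 2.1.3 also stresses genera with a role known from the literature. With only 10 genera tested, the means are 0.19–0.33 and 0.24–0.52. A reader might infer that many false genera are to be expected in this trial. The protocol gives no dominant share and no taxon-metabolite correlation, so it does not support that.

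**The 7.4-point rise in Bacteroidetes in 4.7.1.** A reader might take this as the protocol's own evidence of the artefact's size. It is not: it concerns a phylum, and quitters against continuing smokers, not a genus linked to a metabolite.

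**The analysis is exploratory.** This stands. Table 2 labels the row so, and section 2 calls the investigations largely exploratory. No confirmatory test, arm comparison or sample-size basis depends on it.

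**MOFA is also planned.** It is, but its covariates address confounding rather than the constant sum, its input scale is unstated, and it does not replace the MaAsLin2 and correlation tests.

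**Conclusion.** The point holds in conditional form. On the natural reading of 4.7.5, the tests of taxa against metabolic markers use a constant-sum table. Table 2 adds plain correlation and regression, and the composition-aware method is reserved for arm comparisons. If a dominant taxon is linked to a metabolite, unrelated genera can appear inversely linked, and FDR correction does not remove this.

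The size depends on dominance and link strength, both assumed here. It is about one false genus or fewer near a 20% share with a moderate link, and many only near 40% with rho about 0.5 or near 25% with rho about 0.7. In the last two settings the count is lower when the other genera vary more. Without a link there is no artefact. Dry-weight normalisation does not cure it. The damage would be to the reading of exploratory biomarker links, so this should be corrected before analysis but does not threaten the trial's arm comparisons. Confidence is medium, because the software settings are not shown.

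**What to change.** - In 4.7.5 and the cross-domain row of Table 2, state that taxon-metabolite associations, and those of taxa with craving, emotions or symptoms, use centred log-ratio values of the unrarefied counts. Alternatively, enter the metabolite as the continuous covariate in ANCOM-BC, which the plan already uses and describes as accepting one.
- Detach MaAsLin2 from the rarefied table in 4.7.5, and state its normalisation and transform.
- State the same scale for the microbiome input to MOFA in 4.7.3.
- Reconcile 4.7.5 with 4.7.6.2: either limit dry-weight normalisation to the metabolites, or describe how total bacterial load is measured.

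The log-ratio route needs no new samples, visits or assays, only wording and software settings; measuring total load would add an assay. The downsides are small. Zeros need a stated pseudo-count, and coefficients are read relative to the average taxon. Under extreme dominance, centred log-ratios reduce the artefact but do not abolish it: at share 0.58 and rho 0.7, realised FDR was 0.28 against 0.98 on shares.
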